### Patient and public involvement and engagement

The public interest in the reuse of routinely collected electronic health data for research purposes has expanded over recent years. Our study presents a valuable opportunity to address the challenge of how to develop meaningful and productive patient and public involvement and engagement (PPIE) collaborations in observational studies that make use of secondary data.

We will identify suitable PPIE partners to collaborate on this study and develop creative strategies for meaningful involvement as the project develops. Participants to provide their input that will be particularly valuable for deciding what information would be most useful to patients with diabetes and for providing feedback into the developed diabetes algorithms.

In the latter stages of the study, jointly with our PPIE partners, we will plan and deliver a patients’ and carers’ workshop where we will present emerging findings and seek feedback to inform further work and the dissemination strategy. This will include an exercise around weights of domains within the algorithm. PPIE work will be reported using the GRIPP (Guidance for Reporting Involvement of Patients and Public) checklist.^27^

## Discussion

The global and country-specific prevalence of diabetes has increased substantially.^2 28–31^ For T2DM, prevalence rates have doubled over the past two decades.^4 32 33^ Diabetes diagnosis is associated with higher risk for morbidity and mortality in comparison to people without diabetes.^5^ Despite the natural progression of most chronic diseases, including T2DM, and their important clinical implication on prognosis and medical resources utilisation, only a few studies have attempted to grade the severity of chronic conditions over time. Our proposed study aims to develop a contemporary algorithm to quantify the severity of T2DM, a highly prevalent condition, using routine EHR. The scoring tool will be based on clinically relevant diagnoses and treatments modelled as severity domains and subdomains. The algorithm will enable clinicians to grade patients with T2DM according to the level of their disease severity, at baseline and longitudinally, as driven by the weights of the included clinical domains.

### Prior studies

Currently, there are limited data around validated severity measures that can be used in routine clinical practice managing patients with T2DM. Consequently, we are in parallel finalising a conducted systematic review for clinical-based diabetes severity models which will inform the refinement of this work. Here, we discuss three relevant diabetes severity measures that have been previously reported from countries outside the UK.

In the first study, Gini *et al* categorised the severity of T2DM (n=300) into four levels based on insulin use and the presence of diabetes-related complications (see online supplementary table S3).^15^ A validation study in a random sample of cases was performed by interviewing their GPs. We, however, aim to include more patients with T2DM and consider more clinical data such as other coexisting conditions, non-insulin therapies, statins and ACEIs that have been shown to be associated with reduced risk of adverse outcomes.

In the second study, a diabetes symptom checklist was created to measure the perceived symptom severity and assess the changes over time in 185 patients with T2DM.^16^ The checklist contained 34 items categorised by main clinical symptoms (see online supplementary table S3). The patterns of comorbidities and prescribed treatments were reportedly associated with significant differences in the estimated severity scores.^16^ The sample size was however relatively small and the checklist was based on patients' perception on diabetes symptoms severity.

Third, Young *et al* calculated a Diabetes Complications Severity Index (DCSI) in 4229 patients with type 1 or type 2 diabetes in one US geographic region to examine its association with adverse outcomes (risk of hospitalisation and mortality).^34^ In comparison to using a simple numerical count of complications, DCSI found to be a better tool to predict adverse outcomes. The authors used pharmacy (insulin use only) and laboratory data to compute the severity index and included patients from clinics with largest ethnic diversity (see online supplementary table S3). However, the DCSI missed additional domains such as diabetes duration, hyperlipidaemia and a wider range of diabetes-related and end organ damage manifestations that we aim to assess in addition to hospitalisation and mortality.

In the wider literature, although several studies have investigated the possible role of other various factors on the severity of diabetes, none have provided a severity scoring tool that uses data from various clinical domains as planned in our study that can use the wealth of information routinely collected in electronic healthcare databases. In these studies, approaches used to define diabetes severity included: comparing T2DM severity, before and after obesity surgery;^35^ examining the association between diabetes severity and either haematological and immunological changes,^36^ levels of urine citrate,^37^ a biomarker for adverse outcomes;^38^ grip strength;^39^ or the use of complementary medicine to manage T2DM.^40^

Overall, the severity of T2DM has been previously assessed using the following domains: the complexity of anti-diabetic treatment regimens^35^ or HbA_1c_ levels;^37^ a summary severity variable that includes vascular complications;^41^ or a health status composite, number of comorbidities and patterns of treatments.^42 43^ Other putative and less clinically robust indicators or animal models were reportedly used to assess the severity of T2DM such as the effect of different patient education approaches on diabetes severity;^44^ evaluating the effect of parental history;^45^ and the role of genetic,^46 47^ metabolic^48^ or inflammatory mediators.^49^

In comparison to our planned study, none of the previous studies included as many routinely collected clinically relevant variables as in our more inclusive summary severity score algorithm or assessed the association of estimated scores with the various adverse outcomes included in our defined primary and secondary endpoints.

### Potential strengths and limitations

Our proposed study has several potential strengths: First, it aims to present a contemporary measure to the available tools and the first UK-based study to develop an EHR-based severity scoring tool to grade patients by their T2DM severity. Second, the study uses high-quality real-world medical data routinely collected from general practices. The use of routinely collected data indicates that severity scores can be generated automatically with minimal effort. Third, the views of PPIE collaborators will be incorporated in the development of the severity tool. Fourth, we will access two linked data sets: the hospitalisation (HES) data (to maximise data capture and reduce condition misclassification), and the cause-specific mortality data to ascertain causes of death. Fifth, the sample size is expected to be large enough to drive the development and evaluation of the severity algorithm. Sixth, a statistical validation of the developed algorithm is planned and described.

As we will use data available in CPRD and HES data sets, one of the limitations we anticipate is the possibility to miss other severity indicators not recorded in used data sets. These include detailed pharmacy data such as ‘actual’ dispensing and adherence data. Also, the use of routinely collected data is associated with missing values, being collected from questionnaires, and issues around the accuracy of coding. However, we plan to use appropriate imputation methods and definite criteria to minimise the effect of coding issues. A possible limitation that should be acknowledged is underestimated and poorly represented T2DM severity levels for patients not regularly attending a general practice, people missing appointments or patients not being reliably captured in the database due to very high mobility status (eg, homelessness). This limitation aligns with QOF exception reporting that allows practices to exclude patients from indicators or a clinical domain based on discretionary exception codes. However, the use of QOF exception coding was considered appropriate and its levels were very low, especially for informed dissent.^22^ Another limitation is that our study will be restricted to patients registered with general practices in England, as CPRD currently only provides linkage to external national data sets for consented general practices in England. However, English general practices form the majority of all CPRD practices including nearly 76% of total registered patients.^17^ Finally, due to project time constraints, it is not possible to validate the developed diabetes scores using questionnaires (as reported previously^15^) or replicating the algorithm in a separate data set. However, we have planned a statistical validation of the developed algorithm.

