### Study population

The study cohort will include individuals aged 35 years or over with T2DM (with ≥1 diagnostic code as in (online supplementary table S1) between 1 April 2007 and 31 March 2017. Patients with an ever record of type 1 diabetes (see online supplementary table S2) will be excluded unless they have records of non-insulin anti-diabetic therapies. We chose the study period after 2006 as the quality of CPRD data has improved substantially to adhere with the then introduced important changes to the national incentive scheme The Quality and Outcomes Framework (QOF), an incentivisation programme for all GP surgeries in the UK.^20 21^ QOF exception reporting process allows general practices to exclude patients from indicators or a clinical domain based on discretionary exception codes. However, evidence on the use of exception codes has shown that they are being used appropriately by practices and overall exception rates for diabetes patients are low.^22^

10.1136/bmjopen-2017-020926.supp1Supplementary data

For this cohort construction, we will consider implementing previously validated algorithms designed to identify diabetes cases by avoiding potential misclassification in routinely collected data such as CPRD.^23 24^ Eligible patients will be followed up until censored at the earliest instance of any of the following event dates: patient transferred out of the practice (any cause), last collection date for the practice, the study end on 31 March 2017 or death. The main demographic and clinical characteristics of the defined diabetes cohorts (such as age, gender, geographic region within England, patient-level and general practice-level social deprivation, body mass index (BMI) and baseline glycated haemoglobin (HbA_1c_)) will be identified. Based on our previous studies, the expected sample size in a year will include 11 000 patients with T2DM registered with English general practices linked to the HES Admitted Patient Care data set, HES Outpatient and HES A&E data sets. A random 80% of the identified diabetes cohort (training dataset) will be used to develop the severity tool, with the remaining 20% of the cohort used as a validation data set, as described below.

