#### Severity algorithm validation

When we have developed a first version of the severity score tool, it will be validated statistically by quantifying the association of severity scores to future adverse outcomes. The primary outcome will be developing a cardiovascular event (myocardial infarction, stroke), future hospitalisation and death (diabetes-related mortality, cardiovascular mortality and all-cause mortality). A secondary adverse outcome will be future hospital admission due to hypoglycaemia, a relevant and potentially preventable adverse outcome. Cox proportional hazards (after assessing proportional hazards assumption) and/or competing-risks regressions will be used to perform survival analyses and assess the relationship between the severity score and outcomes controlling for all available patient characteristics (such as age, gender, ethnicity and level of social deprivation). We aim to analyse and assess how severity scores differ across different levels of these variables. As stated earlier, a random 20% of the study cohort (validation data set) will be used to validate the performance of the severity algorithm that was developed in the training data set (80% of the diabetes cohort). Using the calculated subdomains weights (derived by the regression model estimates), Cox regression analysis will be used to validate the developed severity algorithm and we will assess the model performance using relevant measures (such as area under the receiver operating characteristic curve). Using this analysis, we will also test how much the ’sophisticated' full model that includes all relevant severity domains will add in terms of predictive validity of the adverse outcomes over a simpler model that includes demographic data (age, gender and level of social deprivation) alone.

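### Performance is estimated in one random 20% of the cohort; whole-cohort resampling alongside it would cheaply sharpen the estimates for the rarer outcomes, for which the claimed adequacy of the sample is not shown

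*Protocol article*

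**What the plan says.** Under Study population, the protocol article gives one size, based on the authors' previous studies: "the expected sample size in a year will include 11 000 patients with T2DM registered with English general practices". Patients qualify by a diagnostic code dated "between 1 April 2007 and 31 March 2017" and are followed to transfer out, last data collection, study end or death. The same section splits the cohort at random, 80% for development, "with the remaining 20% of the cohort used as a validation data set".

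Under Severity algorithm validation, "a random 20% of the study cohort (validation data set) will be used to validate the performance of the severity algorithm". Performance measures are left open, with the area under the ROC curve (AUROC) as the example. The same analysis is to show how much the full model adds to one holding only age, gender and deprivation. The outcomes are cardiovascular events, hospitalisation, and diabetes-related, cardiovascular and all-cause death. In addition, "A secondary adverse outcome will be future hospital admission due to hypoglycaemia, a relevant and potentially preventable adverse outcome".

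Under Potential strengths and limitations, the article says that "the sample size is expected to be large enough to drive the development and evaluation of the severity algorithm". The same section rules out, for lack of time, both validation by questionnaire and replication in a separate data set.

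**The concern.** The adequacy statement covers both development and evaluation, but evaluation uses only one patient in five. With no replication elsewhere, the hold-out is the only evidence of performance in data not used to build the score.

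For frequent outcomes this probably does no harm. For the rarer ones, the fifth that is analysed may carry too few events to estimate discrimination well. The gain of one model over another is harder still, because it is usually a small difference between two correlated quantities. A wide interval there would leave open whether the severity domains add anything to demographics, although the data to narrow it are already in hand.

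**Working it through.** **Inputs from the protocol article.** 11,000 patients in a year; 20% validation share; a ten-year window. It gives no outcome rate, mean follow-up, total of distinct patients or precision target, so the 11,000 cannot be checked against a sample-size formula.

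**Inputs assumed here.** Event rate 0.1% to 1% per year; follow-up 4 to 6 years; AUROC 0.72; correlation 0.6 between the AUROCs of the two models. The number of distinct patients N is taken as 11,000 (one year's patients are the whole cohort), 30,000 (a middle case) or 110,000 (11,000 new patients in each of ten years).

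**Step 1, size of the hold-out.** 0.20 × 11,000 = 2,200; 0.20 × 30,000 = 6,000; 0.20 × 110,000 = 22,000.

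**Step 2, loss of precision from the split.** At a fixed event rate the standard error of an AUROC varies nearly as 1/√(events). The 20% holds one-fifth of the events, so the ratio of standard errors is √(1/0.20) = √5 = 2.24. This depends on neither the rate nor N. It treats pooled out-of-fold predictions as if they came from one sample of full size, so it is approximate.

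**Step 3, expected events.** Events = n × (1 − exp(−rate × years)). For n = 2,200 at 0.3% per year: 2,200 × (1 − exp(−0.012)) = 26 at 4 years and 2,200 × (1 − exp(−0.018)) = 39 at 6 years.

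**Step 4, precision and power.** The standard error (SE) of each AUROC is by Hanley-McNeil. For the difference between models, SE(diff) = √(2 × (1 − 0.6)) × SE. Power = Φ(gain / SE(diff) − 1.96). At 0.3% per year, for 4 to 6 years:

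| Distinct patients (assumed) | Events in 20% | Power for 0.05 gain, 20% | Power for 0.05 gain, whole cohort |
|---|---|---|---|
| 11,000 | 26-39 | 16-22% | 59-77% |
| 30,000 | 72-107 | 37-51% | 95-99% |
| 110,000 | 262-392 | 87-97% | close to 100% |

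With 2,200 patients the 95% half-width of a single AUROC is 0.09-0.11, against 0.04-0.05 in all 11,000. With 110,000 patients, power for a smaller gain of 0.03 is 46-62% in the 20% and 99-100% in the whole cohort.

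**Step 5, sensitivity to the rate.** With 2,200 patients the 20% holds 9-13 events at 0.1% per year and 86-128 at 1% per year. At 1%, power for a 0.05 gain is 42-57% in the 20% and 98-100% in all 11,000.

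**Step 6, break-even.** One hundred events need 100 / (2,200 × 5) = 9 per 1,000 person-years with five years of follow-up, or 100 / (2,200 × 10) = 4.5 per 1,000 with ten. Below those rates a hold-out of 2,200 has fewer than about 100 events.

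**The case against.** A reader might infer that the validation set has 2,200 patients, that it would yield only tens of events for hypoglycaemia admission and cause-specific death, and that added value therefore could not be judged for them. The article does not support that. The 11,000 is a yearly figure; the split applies to the cohort identified over ten years, patients leave and newly diagnosed ones enter, and so distinct patients should exceed one year's count by an unknown amount. The event counts rest wholly on assumed rates. A cause-specific death rate of 10 per 1,000 person-years (assumed) would give 107 events in 2,200 patients over five years. Imprecision is also a matter of degree. This objection stands.

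It is also fair that the adequacy sentence is hedged and qualitative and promises no power for any single endpoint; that hypoglycaemia admission is a secondary outcome; that the AUROC is only an example and the 0.05 and 0.03 gains are yardsticks chosen here; that the association analyses by Cox or competing-risks regression are not explicitly confined to the 20%; and that a random hold-out is an accepted design. Expected events by outcome are detail that an article may leave to a fuller document, so their absence is not the point.

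Resampling is no complete cure either. At 0.1% per year all 11,000 patients would hold only 44-66 events over 4 to 6 years. Domains chosen by clinical consensus cannot be chosen afresh inside each fold, so some optimism may remain.

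None of this touches Step 2: at any rate and any cohort size, a single split gives up more than half of the attainable precision.

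**Conclusion.** The point holds as a cheap improvement, not as an error in the design. Estimating performance in one random 20% makes standard errors about 2.2 times those available from the whole cohort, and this needs no assumption about event rates or cohort size.

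Whether that matters for a given outcome does depend on assumptions. At 0.3% per year over 4 to 6 years the hold-out would have 26-39, 72-107 or 262-392 events for 11,000, 30,000 or 110,000 distinct patients. Tens of events are thus possible for hypoglycaemia admission, and perhaps for cause-specific death, but not established. For these outcomes the statement that the sample suffices for evaluation is not shown; it is not shown to be false either. All-cause death and any hospitalisation, taken to be frequent, are not affected. Confidence in the practical size is low, because the article gives neither rates nor the total of distinct patients.

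**What to change.** - **Severity algorithm validation:** keep the 20% hold-out. For hypoglycaemia admission and cause-specific death, add 10-fold cross-validated or bootstrap optimism-corrected performance over the whole cohort, including the gain over demographics. Repeat the derivation of the weights in every fold or resample, and report confidence intervals. Report the hold-out result alongside, as a check on optimism from the consensus choice of domains.
- **Study population:** restate the expected size as distinct patients over 2007-2017.
- **Potential strengths and limitations:** limit the adequacy statement to outcomes whose expected events, in the data actually used for evaluation, support it.

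The cost is extra computing and a few sentences. No new data are needed.

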### Importance and the clinical implications of the severity tool

The developed algorithm and severity tool may have significant implications for primary care both in terms of disease management and resource allocation. Ideally, through future work of further validation and assessment of clinical utility, the severity tool will be of practical use in primary care through its implementation in the clinical computing systems used in the UK.^50^ The clinical significance of the developed severity algorithm to primary care is driven by the inclusion of highly relevant clinical domains, such as diabetes-related complications and comorbidities, mapped to routinely collected data.

Additionally, by assessing the longitudinal patterns of severity, the developed tool may be more clinically relevant than the currently used proxy (HbA_1c_), and thus it could be a more reliable indicator in informing practices’ remuneration for diabetes care. Categorising individuals based on their diabetes severity will be relevant for risk stratification (which may enable safer delegation of care within the clinical team), help identify individualised patient risks and will help practitioners triage patients in need of a greater clinical input which informs towards stratified medicine to reduce future life-changing diabetes-related complications. Moreover, the weights of the severity scores may inform future clinical trials as the scoring tool considers a broader range of cardiovascular conditions than in most randomised clinical trials. Given the relatively low rates of cardiovascular outcomes in some trials, identifying patients with diabetes who are at higher risk via our severity algorithm would help to power trials with overall longer-term benefit for patients. Finally, the composite severity score may serve as an important confounding factor in future research, as an example, to match diabetes cases and controls in observational studies and clinical trials.

## Ethics and dissemination

Some data were presented at the annual National Institute for Health Research School for Primary Care Research (NIHR SPCR) Showcase, September 2017, Oxford, UK and at the Diabetes UK Professional Conference, March 2018, London, UK. The study findings will be disseminated in relevant academic conferences and peer-reviewed journals.
